## 1. Trial overview

The REDUSE trial is a multicentre, investigator-initiated, randomized clinical superiority trial comparing protocolized restrictive strategy for the administration of non-resuscitation fluids with usual care in participants with septic shock. Adult patients with septic shock will be eligible for inclusion. Patients will be randomized within 12 hours of admission to the intensive care unit. Participants will not receive maintenance fluids in the intervention arm unless the total fluid volume is insufficient to provide hydration. All intravenous drugs and nutrition will be concentrated to reduce fluid volume. Resuscitation fluids will be administered according to local routines. The intervention will last for the duration of the intensive care unit stay. Participants in the control arm will receive usual care. The primary outcome will be all-cause mortality at 90 days. Secondary outcomes will be complications during ICU stay, cognitive function, health-related quality of life at 6 months, and days alive without mechanical ventilation at 90 days. Healthcare staff involved in the participants' immediate care will not be blinded to the intervention, but participants, outcome assessors, statisticians, manuscript authors and the data safety monitoring committee will be blinded to treatment allocation.

## 2. Background and study rationale

### 2.1 Background

Sepsis is defined as life-threatening organ dysfunction caused by a host response to infection (Singer 2016). Recent estimates suggest that 48 million cases of sepsis occur globally every year and that 11 million sepsis-related deaths occur annually, with the majority of cases occurring in developing countries (Rudd 2020). Septic shock is a subgroup of sepsis with particularly severe circulatory and metabolic abnormalities and 90-day mortality is about 45% (Hernandez 2019, Holst 2014, Meyhoff 2022).

Administration of fluids is an essential component of caring for patients suffering from septic shock (Evans 2021). Fluids are administered for different reasons. Resuscitation fluids are administered intravenously to correct hemodynamic impairment. In contrast, non-resuscitation fluids are administered intravenously and enterally as vehicles for medications and nutrition, to correct electrolyte disturbances, and to ensure adequate hydration (maintenance fluids). The latter purpose is considered to require a total of about 1-2 litres of fluids per day (1 ml/kg/h) in healthy humans and may increase in pathophysiological conditions due to higher than normal losses. More than 50% of patients with septic shock receive 4 L or more of fluids on the first day in the ICU (Marik 2017). This may be adequate in patients with pre-existing deficits, but data suggest that large volumes of fluids are not without risks. Non-randomised studies have indicated that excessive fluid administration might have detrimental adverse effects such as tissue oedema with impaired oxygen delivery and organ function, compartment syndromes and ultimately increased mortality (Boyd 2011, Marik 2017, Silversides 2018, Sakr 2017). This has formed the basis for trials comparing restrictive administration of resuscitation fluids with usual care in adult septic shock patients.

### 2.3 Previous evidence

A recent systematic review with meta-analysis identified 13 trials comparing a restrictive approach of fluid administration with usual care in adult patients with sepsis and/or septic shock (Sivapalan 2023). Twelve of these trials assessed interventions with the objective to

reduce administration of only resuscitation fluids. One trial assessed interventions to reduce resuscitation and non-resuscitation fluids (Chen 2015). A meta-analysis including all 13 trials, showed no difference in mortality (relative risk [RR]: 0.97 [97% CI; 0.86-1.09]), possibly due to small differences in fluid volume between the intervention and control groups.

## 2.4 Rationale for a new trial

Based on data showing that non-resuscitation fluids are the major source of fluid after the first day in the ICU we recently performed a feasibility trial comparing a protocolized reduction of non-resuscitation fluids to usual care in septic shock (Lindén-Søndersø 2019, Lindén 2023, Linden 2024). Our data shows that this approach may reduce the total volume of administered fluids by a median of 3.6 (95% CI; 1.6 to 5.3) L in the first 3 days after inclusion. This reduction is almost twice as large as the most effective protocol targeting the restriction of resuscitation fluids (Meyhoff 2022) and could potentially impact outcomes. In addition, it is unknown whether the balance between benefits and harms of resuscitation fluids differs from that of non-resuscitation fluids. Taken together, a trial powered to detect if restrictive administration of non-resuscitation fluids influences patient-important outcomes is warranted.

## 3. Trial hypothesis and outcomes

The objective is to assess the beneficial and harmful effects of a restrictive strategy for administration of non-resuscitation fluids in adult patients with septic shock.

### 3.1 Primary outcome

- All-cause mortality at 90 days

### 3.2 Secondary outcomes

- One or more complications in the ICU defined as one or more of the following events in the ICU:
  - a) Acute cerebral infarction (documented on brain MRI or CT scans) with corresponding neurological symptoms.
  - b) Acute coronary syndrome (defined as acute myocardial infarction or unstable angina pectoris) AND either reperfusion treatment (percutaneous coronary intervention, PCI or thrombolysis) or initiated/increased antithrombotic treatment.
  - c) Acute intestinal infarction (either diagnosed during surgery or by angiography).
  - d) Limb ischemia (defined as clinical signs of limb ischemia AND one of the following treatments: open or percutaneous vascular intervention, amputation, or initiation/increased antithrombotic treatment.
  - e) New onset severe acute kidney injury (defined as stage 3 according to the kidney disease improving global outcomes [KDIGO] criteria [Kellum 2013]).
- Mechanical ventilation-free days within 90 days of inclusion.
- Cognitive function as determined by the Montreal Cognitive Assessment 7.1 BLIND/telephone version (MoCA-BLIND) at 6 months (Pendlebury 2013, Wittich 2010).

- Health-Related Quality of Life as determined by the EQ Visual Analogue Scale (EQ-VAS) at 6 months (Van Reenen 2015).

### 3.2 Primary environmental outcome

- Climate impact within 90 days after inclusion modelled as Global Warming Potential (GWP) over a 100-year period using a life cycle assessment methodology. GWP is defined as radiative forcing based on the change in concentration of greenhouse gas emissions taking into account the residence time of the substances and is expressed as carbon dioxide equivalents (CO2eq) (Dhalcal 2022).

### 3.3 Explorative outcomes

- Hospital-free days within 90 days of inclusion
- Vasopressor-free days within 90 days of inclusion.
- Renal replacement therapy (RRT)-free days within 90-days of inclusion.
- Major adverse kidney event (MAKE) at 90-days, defined as the composite of mortality at 90 days, initiation of new of renal replacement therapy, or persistent renal dysfunction (defined as a final inpatient creatinine value  $\geq 200\%$  of the baseline value within 90 days)
- Cumulative dose of diuretics during the first 5 days of inclusion, as measured in defined daily doses per the World Health Organization (WHO).
- Glasgow Outcome Scale Extended (GOSE) at 6 months (McMillan 2016).
- European Quality of Life visual 5 dimension-5 level scale (EQ-5D-5L) at 6 months.
- WHO Disability Assessment Schedule (WHODAS) 2.0 (12 item version) total score at 6 months (Üstün 2010).
- Modified Fatigue Impact Scale (MFIS) at 6 months (Téllez 2005).
- All-cause mortality at 12 months.
- Number of days in the ICU within 90 days of inclusion
- Hypoglycaemia (moderate 3.9 - 2.3 mmol/l and severe  $\leq 2.2$  mmol/l) in the ICU
- Hypernatremia ( $> 159$  mmol/L) in the ICU
- Acid base disturbances (hyperchloremic acidosis [ $\text{pH} < 7.15$  and plasma  $\text{Cl}^- > 115$ ], metabolic alkalosis [ $\text{pH} > 7.59$  and  $\text{S-BE} > 9$ ]) in the ICU
- Central venous catheter related complications that could potentially be related to concentrated drugs given in the intervention group (for example, thrombosis, stenosis, malfunction, and infections) in the ICU

For Swedish sites mortality data will be collected from the National board of Health and Welfare.

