### 10.1 Sample size

#### 10.1.1 Primary outcome

The sample size calculation is based on an expected 90-day mortality of 45 % in the control group (Hjortrup 2016, Perner 2012, Hernandez 2019, Holst 2014). To detect an absolute reduction in mortality of 7.5%, with an  $\alpha$  of 5% and a power of 90% the required sample size is 1808. We chose 7.5% as anticipated intervention effect because it is a realistic and clinically relevant effect size observed in previous large intensive care trials assessing interventions in critically ill patients (Perner 2012, Andersen-Ranberg 2023). To account for loss to follow-up and no-consent from some patients we will include a total of 1850 patients.

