| RRT-free days                                           |                        |   |   |   |   |                          | x  |     |     |
| MAKE                                                    |                        |   |   |   |   |                          | x  |     |     |
| Dose of diuretics                                       |                        |   |   |   | x |                          |    |     |     |
| Glasgow Outcome Scale Extended                          |                        |   |   |   |   |                          |    | x   |     |
| WHO Disability Assessment Schedule                      |                        |   |   |   |   |                          |    | x   |     |
| Modified Fatigue Impact Scale                           |                        |   |   |   |   |                          |    | x   |     |
| Number of days in the ICU                               |                        |   |   |   |   |                          | x  |     |     |
| Hypoglycaemia, Hypernatraemia, Acid-base disturbances   | x                      | x | x | x | x | x                        |    |     |     |
| CVC related complications                               | x                      |   | x |   | x |                          |    |     |     |

a) Day 1 one is defined as the day of inclusion.

b) Intervention will only be administered while the patient is in an REDUSE-ICU. If patient is transferred to a non-REDUSE ICU she/he will be considered as discharged from ICU.

RRT= Renal Replacement therapy; MAKE = Major adverse kidney event; CVC = central venous catheter

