#### Up to 90 days after inclusion

- Date of follow-up (dd-mmm-yyyy)
- Status (alive/deceased)
- Days alive and free of renal replacement therapy (RRT) (days; Only include full days without RRT. The data should be recorded for up to 90-days regardless of how the patient was discharged or readmitted.)
- Non-invasive and invasive mechanical ventilation-free days (days; Only include full days without invasive or non-invasive mechanical ventilation. Nasal high flow oxygen therapy is not considered mechanical ventilation. The data should be recorded for up to 90-days regardless of how the patient was discharged or readmitted)
- Vasopressor-free days (days) (Only include full days without vasopressors. The data should be recorded for up to 90-days regardless of how the patient was discharged or readmitted.)
- Days spent in any ICU (days) A day with any time spent in any (incl. non-REDUSE) ICU counts as an ICU day, even if it is less than 24 hours. The data should be recorded for up to 90-days regardless of how the patient was discharged or readmitted.)
- Hospital-free days (days; Only count full days out of hospital. Time spent in a rehabilitation facility, long-stay hospital, hospice, or nursing home is considered as time spent out of hospital. Includes any hospital (even non-REDUSE sites). The data should be recorded for up to 90-days regardless of how the patient was discharged or readmitted)
- ICU-free days (days)
- Creatinine at hospital discharge ( $\mu\text{mol/L}$ ; Latest value recorded within 90 days at any hospital)

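### The explorative count of ICU days is cut short by death, so a difference between arms mixes recovery with survival; days alive and out of the ICU is not a listed outcome

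*Protocol*

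**What the plan says.** Section 3.3 names "Number of days in the ICU within 90 days of inclusion" among the explorative outcomes, and Table 1 has a row "Number of days in the ICU" marked at day 90. Appendix A, under the data collected up to 90 days after inclusion, gives the counting rule: "A day with any time spent in any (incl. non-REDUSE) ICU counts as an ICU day, even if it is less than 24 hours". It does not say how a patient who dies is to be counted.

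The same part of Appendix A collects an item headed "ICU-free days (days" (closing bracket omitted here), with no counting rule and no value for death. No outcome list in sections 3.1 to 3.3, no row of Table 1 and no list in the monitoring committee charter (Appendix B) names it.

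The other 90-day support-duration outcomes are phrased as free days. Ventilation-free days is a secondary outcome; the explorative list has vasopressor-free days, RRT-free days and "Hospital-free days within 90 days of inclusion". Appendix A labels the RRT item "Days alive and free of renal replacement therapy (RRT" (again without its closing bracket), and section 3.4 and the charter describe the ventilation outcome in alive-and-free terms.

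Section 10.1.1 assumes an "expected 90-day mortality of 45 % in the control group" and an absolute effect of 7.5 points. Section 10.2 treats explorative results as generating hypotheses only.

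**The concern.** A patient who dies in the ICU on day 1 contributes one ICU day, the lowest value a participant can have. A patient who recovers and leaves on day 8 contributes eight. The count cannot tell a short stay that ended in recovery from one that ended in death. With 45% of control patients expected to die by day 90, a large share of the counts could be cut short this way, although the protocol does not say how many of those deaths occur in the ICU.

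If the intervention prevents early deaths, the mean stay in that arm may rise with no slower recovery in anyone. If it causes early deaths, the mean stay may fall, and a reader could take the fall for faster recovery or a saving.

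**Working it through.** **Inputs.** From section 10.1.1: control mortality 45%, difference 7.5 points, power 90%, 1808 patients. The protocol gives no ICU stay, ICU mortality or day of death, so every stay and death day below is an assumption.

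**The plan's own figure.** No figure is stated for ICU days. The 7.5-point difference comes from the sample size, which reproduces. With a two-sided alpha of 5% (sidedness assumed), a pooled variance under the null and no continuity correction, n per arm = [1.960·√(2·0.4125·0.5875) + 1.2816·√(0.45·0.55 + 0.375·0.625)]² / 0.075² = 903.3. That rounds up to 904, or 1808 in total.

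**Illustration 1: fixed stays.** Survivors stay S ICU days. The 45% who die in either arm do so in the ICU on day 5. The harmful arm has a further 7.5% who die in the ICU on day D instead of surviving.

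- Control mean = 0.55·S + 0.45·5.
- Harmful mean = 0.475·S + 0.45·5 + 0.075·D.
- Difference in ICU days = 0.075·(D − S).
- Difference in days alive and out of the ICU = −0.075·(90 − S). Here every death is in the ICU, so each death earns zero.
- Difference in 90 minus ICU days, with no death rule = 0.075·(S − D).

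| S | D | Control mean | Harmful mean | ICU days | Days alive and out of ICU | 90 minus ICU days |
|---|---|---|---|---|---|---|
| 6 | 2 | 5.55 | 5.25 | −0.30 | −6.30 | +0.30 |
| 6 | 3 | 5.55 | 5.32 | −0.23 | −6.30 | +0.23 |
| 8 | 2 | 6.65 | 6.20 | −0.45 | −6.15 | +0.45 |
| 12 | 2 | 8.85 | 8.10 | −0.75 | −5.85 | +0.75 |

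On ICU days the harmful arm has the shorter stay. On days alive and out of the ICU it is worse by about 6 days. Taking 90 minus ICU days without a death rule reproduces the distortion with the sign flipped.

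**Illustration 2: constant daily risks.** Each day a patient in the ICU dies with probability d; one who survives the day is discharged with probability r. With ICU mortality p and mean stay T, d = p/T and r = (1 − p)/(T − p). Hold r fixed, so recovery is unaffected, and move ICU mortality to p′. The new mean stay is T′ = p′ + (1 − p′)/r, so a 7.5-point change in ICU mortality moves the mean by 0.075·(1/r − 1).

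- p = 0.30, T = 5.33: r = 0.70/5.03 = 0.139. The shift is 0.46 days, to 5.79 with fewer deaths or 4.87 with more.
- p = 0.35, T = 8.80: r = 0.65/8.45 = 1/13. The shift is 0.075·12 = 0.90 days, to 9.70 with fewer deaths or 7.90 with more.

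This places the whole 7.5 points inside the ICU, although the protocol states it for 90-day mortality.

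**Reversal.** In illustration 1, put the extra deaths on ICU day 15. The difference becomes 0.075·(15 − 12) = +0.23 to 0.075·(15 − 6) = +0.68 days, so the harmful arm now has the longer stay.

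**Timing alone.** Keep mortality at 45% in both arms and move deaths from day 5 to day 2 or 3 in one arm. Mean ICU days change by 0.45·(2 − 5) = −1.35 or 0.45·(3 − 5) = −0.90. Days alive and out of the ICU do not change.

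**The case against.** The strongest reply is that little depends on this item. All primary conclusions rest on 90-day mortality, explorative results only generate hypotheses, and section 11 sends them to separate manuscripts with no substudy published before the main article. Any difference in ICU days would be read with mortality known. No power calculation uses it, and the charter's outcome list omits it. Total ICU days is also a legitimate measure of use in a trial that plans health-economic and environmental analyses, and the statistical analysis plan could separate survivors from non-survivors. All of this stands and keeps the severity low. It does not remove the point: the protocol itself fixes the outcome as a raw count, and a plan that follows it would report a measure confounded with survival.

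A reader might infer four stronger things that the document does not support.

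- That an arm with more deaths is bound to show a shorter stay, or that a successful trial is bound to show a longer one. The direction depends on when deaths occur relative to discharge, which the protocol does not give.
- That this is the only item affected by death. Five-day diuretic dose and the in-ICU events (hypoglycaemia, hypernatraemia, acid-base and catheter complications) are also cut short by death, and Appendix A states no death rule for the hospital-free and vasopressor-free items.
- That the protocol treats fewer ICU days as benefit. It states no direction.
- That listing the existing ICU-free-days field would be enough. It has no death rule, and 90 minus ICU days carries the same distortion.

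**Conclusion.** The point holds as a low-severity weakness in how one explorative outcome is defined. The raw count of ICU days is cut short by death, so a difference between arms cannot be read as a difference in recovery. For a 7.5-point mortality difference, the two illustrations give shifts of about 0.2 to 0.9 days in mean stay. Those figures assume survivor stays of 6 to 12 days with extra deaths on day 2 or 3, or ICU mortality of 30 to 35% with control mean stays of 5.33 to 8.80 days and unchanged discharge. None of these values is in the protocol, and late deaths can reverse the sign. Size and direction are therefore illustrative; only the mixing of recovery with survival follows from the definition itself.

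**What to change.** In section 3.3 and Table 1, name days alive and out of the ICU within 90 days of inclusion as the outcome. In Appendix A, give the ICU-free-days item a counting rule and state that days after death earn no credit. It can be derived as days alive up to day 90 minus days spent in any ICU, using the ICU-day item and the date of death, both already collected. The treatment of part-days and of the day of death should be stated so that the two counts agree.

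Keep total ICU days as a resource-use measure, reported separately for survivors and non-survivors.

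The cost is one or two lines of text and one derived variable; no new data are needed.

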### 3.4 Rationale for primary and secondary outcomes

Several observational studies have reported an association between a positive cumulative fluid balance and mortality (Boyd 2011, Marik 2017, Sakr 2017, Silversides 2018).

Because less administration of non-resuscitation fluids could decrease intravascular volume and therefore increase ischemia and acute kidney injury, we will assess the incidence of ischemic complications and acute kidney injury. Previous trials assessing effects of restrictive

administration of resuscitation fluids in sepsis have found no effect or a decreased incidence of acute kidney injury (Douglas 2020, Hjortrup 2016, Meyhoff 2022)

Days alive and free of mechanical ventilation is a patient-important outcome and is also essential to assess potential effects on healthcare costs. Strategies to reduce fluid overload in patients suffering from acute respiratory distress syndrome have been suggested to increase the number of days alive and free of mechanical ventilation (Wiederman 2006).

Cognitive impairment and decreased HRQoL are common after sepsis (Hammond 2020, Iwashyna 2013, Kjær 2023). Restrictive fluid administration has been associated with impaired cognitive function in patients suffering from acute respiratory distress syndrome (ARDS) (Mikkelsen 2012). No differences in HRQoL and cognitive function could be demonstrated by restricting resuscitation fluids in septic shock in the recent CLASSIC trial but clinically important differences could not be excluded (Kjær 2023). Based on a modified Delphi process involving patients and researchers (<http://www.improvelto.com>), the performance-based cognitive screening measure MoCA and the patient-reported outcome measure EQ-5D-5L have been the recommended tests for cognitive function and HRQoL in patients with acute respiratory failure, a common organ failure in septic shock (Needham et al 2017). These tests have been used in large trials in septic shock and have been translated into many languages including Swedish (Kjær 2023, Hammond 2020).

#### **4. Eligibility**

Patients will be eligible for inclusion if they fulfil all of the inclusion criteria and none of the exclusion criteria.

##### **4.1 Inclusion criteria**

- Adult ( $\geq 18$  years of age)
- Septic shock according to the Sepsis 3 criteria (Singer-16) at any time within 12 hours after ICU admission (suspected or confirmed infection, plasma lactate above 2 mmol/L, and use of vasopressor to maintain mean arterial pressure of 65mmHg or above after receiving adequate fluid resuscitation [ $> 1L$  within 12 h of screening]) and ongoing vasopressor therapy at the time of screening.

##### **4.2 Exclusion Criteria**

- Confirmed or suspected pregnancy
- Previous inclusion in the REDUSE-trial
- Screened more than 12 hours after ICU admission.

##### **4.3. Note on inclusion and exclusion criteria**

Patients with septic shock receive large amounts of fluids and they are the patient category in which an association between a positive fluid balance and a poor outcome has been consistently observed in observational studies. Patients with septic shock have a high mortality and are the most common group of critically ill patients in which large volumes of fluids are administered. Hence, this is a patient group in which the intervention is expected to have the greatest effect.

Patients readmitted to the ICU during the same hospital stay will remain in the same study arm to which they were initially allocated regardless of diagnosis. Patients readmitted to the ICU after discharge from hospital will not be eligible for inclusion.

